## Abstract

**Background:**

Low anterior resection for rectal cancer is commonly associated with a diverting stoma. In general, the stoma is closed 3 months after the initial operation. The diverting stoma reduces the rate of anastomotic leakage as well as the severeness of a potential leakage itself. Nevertheless, anastomotic leakage is still a life-threatening complication and might reduce the quality of life in the short and long term. In case of leakage, the construction can be converted into a Hartmann situation or it could be treated by endoscopic vacuum therapy or by leaving the drains. In recent years, endoscopic vacuum therapy has become the treatment of choice in many institutions. In this study, the hypothesis is to be evaluated, if a prophylactic endoscopic vacuum therapy reduces the rate of anastomotic leakage after rectal resections.

**Methods:**

A multicenter parallel group randomized controlled trial is planned in as many as possible centers in Europe. The study aims to recruit 362 analyzable patients with a resection of the rectum combined with a diverting ileostoma. The anastomosis has to be between 2 and 8 cm off the anal verge. Half of these patients receive a sponge for 5 days, and the control group is treated as usual in the participating hospitals. There will be a check for anastomotic leakage after 30 days. Primary end point is the rate of anastomotic leakages. The study will have 60% power to detect a difference of 10%, at a one-sided alpha significance level of 5%, assuming an anastomosis leakage rate of 10%–15%.

**Discussion:**

If the hypothesis proves to be true, anastomosis leakage could be reduced significantly by placing a vacuum sponge over the anastomosis for 5 days.

**Trial registration:**

The trial is registered at DRKS: DRKS00023436. It has been accredited by Onkocert of the German Society of Cancer: ST-D483. The leading Ethics Committee is the Ethics Committee of Rostock University with the registration ID A 2019–0203.

## Background

Despite all progress in improving the treatment of patients with rectal cancer with neoadjuvant therapy or total mesorectal exzision (TME), anastomosis leakage (AL) after low anterior resections remains a significant problem. The rate of insufficient anastomosis lies between 0% and 26% (1, 2). Up to 2007, the treatment of AL was limited to converting into a Hartmann situation, reoperation, or treating the patient with an intelligent regime containing the component drainage, rinsing, and diverting stoma. The diverting stoma itself led to a decrease of AL and lowered mortality (3, 4).

In 2008, Weidenhagen et al. (5) published their results of a new approach for AL by using an endoscopically placed vacuum sponge (EVT) in the insufficient cavity and a commercial system became available. This system leads to a high percentage of successful healing of AL. Until now, there is no randomized trial available comparing the results of conventional treatment vs. the EVT. Kühn et al. (6) compared their results of EVT with a historical cohort of conventionally treated AL and found a significantly higher success rate of EVT compared to conventional treatment (95.2% vs. 65.9%, *p* = 0.011). EVT was also associated with the preservation of intestinal continuity in a significantly higher percentage of patients than those undergoing conventional treatment (86.7% vs. 37.5%, *p* = 0.001).

In many hospitals in Germany and other countries, EVT for treating AL is considered the gold standard and the results are satisfying (7, 8). However, the treatment is costly and time-consuming. It might be even better if AL could be avoided in the first place. Despite attempts testing the anastomosis intraoperatively and the blood flow of the two sides of the rectum and descendens, the intraluminal placement of a vacuum sponge might lead to a significantly reduced rate of AL.

### Objectives and hypothesis

The aim of our study was, therefore, to investigate whether an intraoperatively placed sponge reduces the rate of AL compared with patients treated without sponge after rectal resection.

## Methods

The administrative and medical processes are shown in flowcharts 1 and 2.

### Design

A prospective randomized multicenter clinical superiority trial is performed with a balanced randomization. Before the inclusion of the first participant, the trial was evaluated by the Ethics Committee of Rostock University (ID: A 2019–0203). Then, the trial was registered at DRKS (DRKS00023436). It has been accredited by Onkocert of the German Society of Cancer (ST-D483).

During the course and additional centers joining the study, there were positive statements of the following ethics committees: Medical Association of Saxony, Thuringia, Westfalen-Lippe, Bavaria, Baden-Württemberg, and of the Universities of Wuppertal and Düsseldorf.

### Participants and recruitment

Individuals referred to one of the participating centers for rectal resection will be examined and screened for potential participation. Recruitment will be performed in a standard outpatient or inpatient clinic setting by a surgeon at least 24 h before the operation. Information about the study is handled over to the patient and formal consent was obtained.

### Randomization

After the written consent is signed, the participating hospital will contact the study center transferring a form asking for randomization. For each participating hospital, 10 lots with equal number for treatment and control lots are objected. One of these lots is drawn every time a participating center requests for randomization. The result of randomization is transferred back until 8 a.m. the next morning the latest.

### Surgery and EVT

Surgery itself is performed as usual in the participating center. There are no rules given by the study. After finishing the operation, a sponge should be placed in the treatment group endoscopically *via* rectoscopy or palpatory method with the center of the sponge lying on the intraluminal anastomosis. The sponge parameters are 100–125 mmHg suction with medium intensity and continuous suction. After 5 days, the suction is turned off and the sponge is removed without checking the anastomosis generally.

All other treatments are done as usual in the participating center. Further treatment after the operation is documented in a standardized documentation form including questions of searching for AL and potential treatment of AL.

There will be a check for anastomotic leakage after 30 days. A questionnaire will be completed *via* telephone or during a planned check up in the office. Indicators for AL include secretion of pus or blood transanally, pain, fever, etc. In all of these cases, the participating hospital takes action to search for AL. Primary end point is the rate of anastomotic leakages. Secondary end points are the quality of TME and the method of treating AL.

### Sample size and statistical analysis

The sample size was calculated with G-Power 3.1. The study will have 60% power to detect a difference of 10%, at a one-sided alpha significance level of 5%, assuming an anastomosis leakage rate of 10%–15%.

Altogether, 362 patients have to be analyzed.

Statistical analysis will be performed using Statistical Package for Social Science (SPSS) version 23.0. All data are regularly transferred from the documentation forms to the database. Statistical analysis will be done using Pearson's *χ*^2^ test (Fisher's exact test).

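### The stated 60% power for a 10% difference does not follow from 362 patients: a 10-point reduction from a leak rate of 10–15% has about 93% to over 99% power

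*Protocol article*

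**What the plan says.** The section on sample size and statistical analysis gives the whole justification in a few sentences. "The sample size was calculated with G-Power 3.1". The claim is "The study will have 60% power to detect a difference of 10%, at a one-sided alpha significance level of 5" per cent, "assuming an anastomosis leakage rate of 10%–15" per cent, and then "Altogether, 362 patients have to be analyzed". The abstract repeats the power claim and the number: "The study aims to recruit 362 analyzable patients".

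Three other statements fix the setting of the calculation:

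- The Design section describes a "clinical superiority trial is performed with a balanced randomization", so 362 means 181 per arm.
- The analysis is Pearson's chi-square test, with "Fisher's exact test" in brackets, so two proportions are compared.
- The objective is to "investigate whether an intraoperatively placed sponge reduces the rate of AL compared with patients treated without sponge", so the effect sought is a reduction in the sponge arm.

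The article does not say which arm the 10–15% belongs to, whether the 10% difference is absolute or relative, or which test family and effect size were entered in the software.

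**The concern.** This is the only justification given for the size of the trial. It states sample size, alpha, sidedness, difference, event rate and power, so it can be checked. Since the aim is a reduction, 10–15% reads most naturally as the control rate and 10% as an absolute difference. The effect is then 15% to 5% at one end and 10% to 0% at the other. Differences of that size at low event rates are easy to detect with 181 patients per arm, so a power of only 60% looks wrong at once.

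At stake is what the trial can be said to detect. The stated effect may be the intended one, in which case the power figure is much too low. Or a different, smaller effect was intended, and the sentence does not describe it. A reader of the final result needs to know which.

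**Working it through.** **Inputs.** n = 181 per arm (362 divided equally), one-sided alpha 0.05 (z = 1.645), control rate p1, sponge rate p2, mean rate p = (p1 + p2)/2.

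**Formula (normal approximation to the chi-square test).** Power = Φ[(p1 − p2 − 1.645·s0)/s1], where s0 = √(2p(1 − p)/n) and s1 = √((p1(1 − p1) + p2(1 − p2))/n).

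**Attempt to reproduce the stated 60%, 15% to 5%.** p = 0.10.
- s0 = √(2 × 0.10 × 0.90/181) = 0.03154
- s1 = √((0.1275 + 0.0475)/181) = 0.03109
- (0.10 − 1.645 × 0.03154)/0.03109 = 1.548, so power = 93.9%

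**10% to 0%.** p = 0.05.
- s0 = 0.02291, s1 = 0.02230
- (0.10 − 0.03768)/0.02230 = 2.79, so power = 99.7%

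The stated 60% is not reproduced at either end.

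**All readings, 181 per arm, one-sided 5%.** The exact columns sum binomial probabilities over every pair of leak counts for which the test rejects.

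| Reading | Control → sponge | Approximation | Exact chi-square | Exact Fisher |
|---|---|---|---|---|
| 10 points, 10–15% is the control rate | 15% → 5% | 93.9% | 94.7% | 92.7% |
| | 12.5% → 2.5% | 97.7% | 98.7% | 97.7% |
| | 10% → 0% | 99.7% | about 100% | about 100% |
| 10 points, 10–15% is the sponge rate | 20% → 10% | 84.8% | 85.4% | 82.0% |
| | 25% → 15% | 77.0% | 77.4% | 73.5% |
| 10–15% names the two arms | 15% → 10% | 41.8% | 41.7% | 36.1% |
| 5 points from 10% | 10% → 5% | 56.4% | 56.8% | 49.3% |
| Relative 10% | 15% → 13.5% | 10.8% | 10.8% | 8.4% |

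**Sample size that 60% power would need.** n per arm = [1.645·√(2p(1 − p)) + 0.253·√(p1(1 − p1) + p2(1 − p2))]²/(p1 − p2)².
- 15% → 5%: 64.6, so 65 per arm, 130 in total
- 10% → 0%: 34 per arm, 68 in total
- 15% → 10%: 315.04, so 316 per arm, 632 in total

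None of these is 362.

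**Effect for which 181 per arm does give 60%.** Solving the power formula for p2 gives 15% → 8.6% (6.4 points), 12.5% → 6.6% (5.9 points) and 10% → 4.8% (5.2 points). At the rounded rates, exact chi-square power is 59.7% for 15% → 8.6% and 60.3% for 10% → 4.8%. Fisher's exact test gives 53.8% and 52.7%.

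**Where 362 may come from.** A one-sided two-sample t-test at alpha 5% with standardised difference d = 0.2 has noncentrality 0.2·√(n/2). Its power is 59.83% at 180 per arm and 60.03% at 181, so 60% is first reached at 181 per arm, which is 362 in total. A one-degree-of-freedom chi-square test with w = 0.1 reaches 60% at 361, but only with its alpha set to 0.10, the equivalent of one-sided 5%.

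**The case against.** The strongest defence is that the article does not define its terms fully, so some reading might give 60%. One comes close: 25% to 15%, tested two-sided with Fisher's exact test, has 61.7% power. It contradicts the stated one-sided alpha and puts the control rate well above 10–15%. A difference of 55% against 45% gives 60.2% one-sided, but lies nowhere near the stated rates. The reading 10% to 5%, at about 57% by chi-square, is also near 60%, but it is a 5-point difference. None of these rescues the sentence.

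The defence does stand on four points, where a reader might infer more than the documents support:

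- *That the trial is underpowered.* For an absolute 10-point reduction the sentence understates power. Power is well below 60% only if a smaller effect was intended, such as 15% to 10% or a relative 10%. Because the article does not give the intended effect, it cannot be said that a null result would be misread.
- *That 362 was computed for a generic small effect.* The match with d = 0.2 is exact, but it is not the only setting that gives about 60%, and the article reports neither the test family nor the effect size. The origin is probable, not documented.
- *That the detectable effect is half the stated one.* At 60% power it is 5.2 to 6.4 points, or 52% to 64% of the stated 10.
- *That the sentence can be repaired by quoting 8.6% and 4.8% as the target rates.* Nothing in the article supports these as chosen targets, and the 60% attached to them holds for the chi-square test only.

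**Conclusion.** The power statement is wrong as written, in the abstract and in the methods. With 181 patients per arm and a one-sided 5% test, a 10-point reduction from 15% has about 94% power by chi-square (93% by Fisher). From 10% it has over 99%, but this requires essentially no leaks in the sponge arm, and the Limited results section already reports two there. No one-sided reading of a 10-point difference at or near the stated rates gives 60%.

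The conclusion assumes equal arms of 181 and an analysis by one of the two tests named. It does not depend on how 362 was obtained. Whether the trial has more or less power than its investigators intended cannot be settled from the article, because the intended effect is not stated unambiguously.

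**What to change.** Replace the power sentence in the abstract and in the sample size section. The new sentence should state:

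- the intended leak rate in the control arm and in the sponge arm,
- that the difference is absolute,
- the test used (Pearson's chi-square or Fisher's exact),
- the power that 362 analysed patients give for that effect with that test.

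For reference, with 181 per arm and a one-sided 5% Pearson chi-square test, power is about 94% for 15% to 5% (93% with Fisher). It is about 60% for 15% to 8.6% or 10% to 4.8% (about 53–54% with Fisher). If the intended effect is smaller, such as 15% to 10%, state its true power of about 42% (36% with Fisher). Reaching even 60% for that effect would take about 632 patients.

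Correcting the statement costs one sentence in two places and no extra patients. Whether 362 remains the right number is for the investigators to decide once the intended effect is stated.

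### Lots are balanced within hospital but the named primary test ignores hospital: valid, mildly conservative if leak rates differ between hospitals, and a small avoidable loss of power

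*Protocol article*

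**What the plan says.** The Design section states: "A prospective randomized multicenter clinical superiority trial is performed with a balanced randomization". The Randomization section gives the mechanism: "For each participating hospital, 10 lots with equal number for treatment and control lots are objected", and then "One of these lots is drawn every time a participating center requests for randomization". Allocation is therefore organised hospital by hospital, in sets of ten lots with five for each arm.

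Under Surgery and EVT, the study sets no rules for the operation, and the rest of care is local too: "All other treatments are done as usual in the participating center". After the 30-day questionnaire, the search for a leak is also left to the hospital. The outcome is binary: "Primary end point is the rate of anastomotic leakages".

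The section Sample size and statistical analysis names one method: "Statistical analysis will be done using Pearson's" chi-square test, with Fisher's exact test in brackets. It mentions no stratification or adjustment by hospital. The same section says "The study will have 60% power to detect a difference of 10"%, "at a one-sided alpha significance level of 5"%, with an assumed leakage rate of 10–15% and 362 patients to be analysed.

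**The concern.** If allocation is balanced within hospital, differences between hospitals cancel out of the comparison of arms. An unstratified 2×2 test does not know this and still counts those differences as random error. Its standard error is then somewhat too large, its true type I error falls below the nominal level, and it has less power than a test stratified by hospital on the same data.

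The protocol makes hospital differences plausible: surgical technique, aftercare and the work-up for leakage all follow local practice, and the Background cites leakage rates from 0% to 26%. At stake is a modest amount of power in a trial that cannot easily add patients. The risk of a false claim of benefit is not increased.

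**Working it through.** **Inputs from the protocol.** Ten lots per hospital, five per arm; 362 analysed, so 181 per arm; one-sided 5%; 12 of 73 randomised patients excluded so far (12/73 = 16%).

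**Assumptions.** Lots are drawn without replacement and a new set of ten follows the tenth lot (neither is stated). There are 9 to 40 hospitals. Hospital effects are normal on the logit with SD 0 to 1.3. The pair 15% vs 5% is one reading of a 10-point difference. The pairs 15% vs 10%, 10% vs 5% and 15% vs 8.4% are not in the protocol; the last is used only because it puts power near 60% at this size.

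**Step 1: the plan's own figure.** Pooled-variance formula:

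n per arm = [z₀.₉₅·√(2p̄(1−p̄)) + z₀.₆₀·√(p₁(1−p₁)+p₂(1−p₂))]² / (p₁−p₂)²

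For 15% vs 5%: [1.645·√0.18 + 0.253·√0.175]² / 0.01 = 64.6, so 65 per arm and N = 130. For 20% vs 10%, N = 184. Neither is 362. Conversely, 181 per arm gives 94% power for 15% vs 5% and 85% for 20% vs 10%. For 5-point differences it gives 42% (15% vs 10%) and 56% (10% vs 5%). The 60% therefore does not describe a 10-point difference at the stated rates, and the size of the present point has to be judged at several effects.

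**Step 2: direction, by hand.** The overall binomial variance splits as p̄(1−p̄) = mean of pₕ(1−pₕ) + variance of pₕ across hospitals. With balance within hospital, only the first term affects the difference between arms, but the unstratified test uses both. Illustration: half the hospitals at 5% and half at 25%, mean 15%.

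- Within-hospital variance: (0.0475 + 0.1875)/2 = 0.1175.
- Between-hospital variance: 0.10² = 0.0100.
- Total: 0.1275.
- True size at nominal 5%: P(Z > 1.645·√(0.1275/0.1175)) = P(Z > 1.713) = 4.3%.

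**Step 3: simulation.** Unstratified: z = (p_C − p_T)/√[p̄(1−p̄)(1/n_C + 1/n_T)]. CMH without continuity correction: z = Σ(xᵢ − tᵢn_Cᵢ/mᵢ) / √Σ[n_Cᵢn_Tᵢtᵢ(mᵢ−tᵢ)/(mᵢ²(mᵢ−1))], where for hospital i x is control leaks, t all leaks and m all patients. There were 20,000 to 40,000 runs per setting.

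One-sided size at nominal 5%:

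| Hospital SD | Unstratified |
|---|---|
| 0 | about 0.050 |
| 0.5 | 0.045–0.050 (one cell 0.054, simulation noise) |
| 0.8 | 0.041–0.049 |
| 1.2 | 0.037–0.044 |

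CMH stays at about 0.046–0.054 throughout.

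Power gain of CMH with equal hospitals and complete blocks (9, 18 or 36 hospitals):

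| Hospital SD | Gain, points |
|---|---|
| 0 | about 0 to 0.5 |
| 0.5 | 0.3 to 1.2 |
| 0.8 | 0.5 to 2.6 |
| 1.2 | 0.9 to 5.5 (largest: 15% vs 10%, 40.8% to 46.3%) |

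Near 60% power (15% vs 8.4%, 18 hospitals of 20), unstratified against CMH: SD 0.5, 61.8% vs 63.0%; SD 0.8, 62.2% vs 64.4%; SD 1.0, 62.1% vs 65.0%; SD 1.3, 62.3% vs 66.6%. At 15% vs 5% the gain is 1 point or less.

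**Step 4: a less tidy layout.** Uneven hospitals, incomplete blocks, 431 randomised with 16% excluded (431 × 0.84 = 362). Over 10, 20 and 40 hospitals, unpooled CMH changes power by −2.1 to +4.2 points. The worst case is 40 hospitals with SD 0 at 10% vs 5% (57.3% vs 55.2%).

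**Step 5: pooling.** 40 uneven hospitals near 60% power, with hospitals under 10 patients pooled into one stratum:

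| Hospital SD | Unstratified | Pooled CMH | Difference, points |
|---|---|---|---|
| 0 | 62.2% | 61.7% | −0.5 |
| 0.5 | 62.6% | 62.8% | +0.2 |
| 0.8 | 63.7% | 64.9% | +1.2 |
| 1.2 | 61.6% | 64.6% | +3.0 |

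**The case against.** The strongest reply is that nothing here threatens validity. The named test holds its level, so what remains is a preference about efficiency. That is right, and it limits the severity. A reader might infer that ignoring hospital inflates the false-positive rate; the calculation shows the opposite.

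Second, the gain depends on layout and on unknowns. The protocol gives neither the number of hospitals nor the variation between them. It wants as many centres as possible, and the Design section lists eight ethics committees against 73 randomised patients, about 9 each, so many hospitals may not fill a set of ten. With 40 small hospitals and little heterogeneity, an unpooled CMH test is the weaker one. This stands against an unpooled test, but pooling small hospitals removes most of the loss.

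Third, a reader might take the stated 60% power as making the loss urgent. The documents do not support that: 362 does not follow from the stated inputs, and at 15% vs 5% power is about 94%. The sample-size mismatch is the larger fault in that section. Using Fisher's exact test also costs more than omitting hospital (42% to 36% at 15% vs 10%; 56% to 49% at 10% vs 5%).

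Fourth, adjustment for centre is often left to an analysis plan, which is not shown here and may already contain it. The article therefore cannot be read as proving that no adjusted analysis exists. But it does name a test, and that test does not match the randomisation it describes, so the point is about what is stated.

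Finally, balance within hospital requires drawing without replacement, which is not stated. A set of ten equally split lots secures balance only on that reading.

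**Conclusion.** The point holds as a low-severity matter of efficiency. The stated test does not use the stratification built into the stated randomisation. If hospitals differ, the one-sided size is roughly 4–5% instead of 5%. For SDs of 0.5–1.2 on the logit, the power forgone is about 0–3 points near 60% power, up to about 5 with extreme variation and complete blocks, and 1 point or less at 15% vs 5%. If hospitals hardly differ, nothing is lost.

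The mismatch is clear from the text, subject to drawing without replacement, and the direction is firm once leak rates differ. The size is conditional, because the hospital SDs, the number of hospitals and the effects below 10 points are assumptions.

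**What to change.** Replace the sentence on the test with one that makes the primary analysis a CMH test stratified by hospital, without continuity correction. Hospitals below a pre-set size (for example, fewer than 10 analysed patients) form one pooled stratum. Report the Mantel–Haenszel risk difference, Σwᵢ(p_Cᵢ − p_Tᵢ)/Σwᵢ with wᵢ = n_Cᵢn_Tᵢ/mᵢ, with its confidence interval. Keep the unstratified chi-square as a sensitivity analysis. State also that lots are drawn without replacement and what follows the tenth lot, since the stratified analysis relies on this.

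The cost is a sentence or two; CMH is standard in SPSS, and no patients or data are added. The downside is a loss of up to about 1 point of power if hospitals do not differ. The change should be fixed before further comparative results are seen: the Limited results section already reports leaks by arm (four control, two treatment, among 47 patients), so a later change of test could look data-driven.
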